Data collection will be conducted in a clinical setting for baseline, when the child is 4-6 months (CF1), 9 months of age (CF3), and 12 months of age (CF6). Additionally, brief monthly questionnaires administered over the telephone or as a face-to-face interview will collect information on the dietary intervention adherence and recent health history.

**Questionnaires** (baseline, CF1, CF3, CF6)

From 4 to 6 months, brief monthly questionnaires will determine breastfeeding, formula feeding, and whether/what solids have been introduced. Brief exit interviews will determine participant burden and suggestions to improve engagement with the intervention.

**Anthropometry** (baseline, CF1, CF3, CF6):

Standardised anthropometric measurements will include weight and length. Measurements will be performed using calibrated age-appropriate instruments, including electronic scales and measurement mat with the children wearing light or no clothing. Measurement accuracy will be monitored by two parameters, the degree of refinement (recorded to 0.5 cm or 0.1 kg) and the degree of tolerance (measurement agreement between 1 cm and 0.1 kg). Three serial measurements from each infant will be calculated. Prior to the measurement of weight, infants will be required to have a nappy change if soiled.

**Diet** (CF1, CF3, CF6):

Adherence to the food targets will be determined by daily retrospective questionnaires, product counts, and photographs of food offered and waste. Dietary intake will be measured at CF1, CF3, and CF6 using 3-day weighed food records. Breast milk remains an important component of the diet during the age period in question, and has important impacts on both the GI microbiota and immune function. Breast milk volume will be measured. Infant formula can be captured directly by the diet record.

**Blood** (CF1 and completion):

Specific consent will be sought to collect two blood samples (CF1 and CF6). The blood sample will be collected by a trained phlebotomist and will be used to assess the following:

- The protective antibody response in plasma following the oral rotavirus which is administered in the standard immunisation schedule at 6 week, 3 months, and 5 months of age. (Isolauri 1995)
- The protective antibody response in plasma following the intramuscular pneumococcal vaccination which is administered at 6 weeks, 3 months, 5 months, and 15 months of age. (Bunout 2004, Perez, 2010)

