A plasma sample will be obtained for global metabolite profiling and total antibody titres in plasma will be assessed at 6, 9 and 12 months as a non-specific measure of protective antibody responses.

Peripheral blood mononuclear cells will be isolated to perform B cell receptor (BCR) repertoire analysis. The total antibody repertoire encoded by B cells is continuously shaped by exogenous as well as endogenous factors, such as vaccines [Galson 2014] and the GI microbiota [Wesemann 2015], both key variables in the study. The high-throughput analysis of the BCR repertoire, by means of next-generation deep sequencing of the immunoglobulin heavy chain complementary determining region (CDR) [Perez 2010], will provide the necessary depth of analysis to detect potential changes in the clonal diversity of individual antibody repertoires while changes to the microbiota are being made via the proposed nutritional intervention [Boyd 2016, Georgiou 2014].

**Urine** (baseline, CF1, CF3, and CF6)

Urine samples will be taken at collected at 6, 7.5, 9 and 12 months for global metabolite profiling. Clean catch urine samples are the recommended method for urine collection. If not available, other non-invasive methods such as the use of urine collection pads should be used (NICE Guidelines). Parents/caregivers will be provided with all necessary equipment for the successful collection and storage of urine samples. Collection pads for obtaining urine specimens from young children, such as the Euricol® Newcastle Urine Collector (UK). Sample collection will be as follows: parents/caregivers must ensure that the participating child’s genital area is clean and dry (using un-medicated products). The collection pad is applied to the area where urine is voided, i.e. in an infant, the pad can be kept in place with a disposable nappy fitted inside out (so that there is no potential for the nappy to absorb the urine). The pad should be checked every 10 minutes to see if it is wet. If no urine is collected after 30 minutes then a new pad should be applied. Following successful collection on the pad, a syringe should be used to draw urine up out of the pad. Samples should be transported to the clinic within a short time frame, or can be stored in a refrigerator and processed appropriately.

**Stools** (baseline, CF1, CF3, and CF6)

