Faecal samples will be collected at 6, 7.5, 9 and 12 months of age according to a pre-defined protocol. Faecal samples will be used to assess the extent to which the complementary feeding has modulated the infant GI microbiota and to quantify vaccine-specific antibody responses as a non-specific measure of protective antibody responses. Parents/caregivers will be provided with all necessary equipment for the successful collection and storage of stool samples from their infants nappy e.g. gloves, sterile sample container with scoop for the stool sample, zip lock bag, polystyrene box, freezer gel pack, and a rubbish bag. Parents/caregivers will collect samples from the nappy after the participating infant has passed a bowel motion. Scoops present in the sample container will transfer approximately 1 tsp of the stool sample into the sterile tube. Once the lid is secure, the sterile tubes will then be placed in the zip lock bag together with the frozen gel pack and placed in the polystyrene box provided. Samples can be kept at room temperature in the polystyrene box and brought into the pre-arranged clinic appointment within 24 hours.

**Saliva** (baseline, CF1, CF3, and CF6)

Saliva samples will be collected to quantify vaccine-specific antibody responses at 6, 9 and 12 months of age as a non-specific measure of protective antibody responses. Samples will be collected according to a pre-defined protocol. Saliva will be collected using a Salivette. The cotton wool swab is removed from the salivette and placed in the infant’s mouth until saturated (1 to 3 mins). This is achieved through rolling the swab inside the child’s cheek. The swab is replaced in the salivette and capped. Once prepared, samples will be stored at -80°C until analysis.

**Breast Milk** (baseline, CF1, CF3, and CF6)

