3. Milestone 2: Best method(s) to collect data on adherence to consuming the candidate foods (number attempted, number completed, quality).
4. To determine the feasibility of the outcome measurements (infection, immune, microbiome, host/microbe metabolome), assess recruitment potential, and identify high prevalence adverse events.
5. Milestone 1: Feasibility of measuring protection against infection using daily parental report of infection (number attempted, number completed, quality).
6. Milestone 2: Feasibility of measuring immune response to the rotavirus and pneumococcal vaccines in venepuncture blood and saliva as measures of immune function (% of children who followed the immunisation schedule, % of parents who agree to blood test, % successful blood draws in young children, data fit to purpose).
7. Milestone 3: Feasibility of using medical records as a measure of immune response
   (% of parents who agree to data access, completeness of data access, data fit to purpose).
8. Milestone 4: Feasibility and logistics of collecting 4 faecal samples between 6 and 12 months of age (number collected).
9. Milestone 5: Recruitment rate per month and extent and type of advertising required.
10. Milestone 6: Prevalence and nature of parent-reported adverse events, and identification of gross changes in growth rate.
11. To determine an appropriate sample size for the proposed full clinical trial.
    1. Milestone 1: Sample size required for the primary objective of the proposed clinical trial – improved immune protection from infection as a result of consuming the candidate food(s).
    2. Milestone 2: Sample size required for the secondary objective of the proposed clinical trial – altered microbiota as a result of consuming the candidate food(s).

Research Plan (2019 – 2024)

The present proposal aims at delivering the scientific insight and development concept to enable design and execution of a follow-up full clinical trial, informed by the pilot trial described in the present submission. The full-scale clinical study will test whether and how immune protection benefits can be conferred to infants around the weaning period by “targeted prebiotic feeding”. In contrast to the pilot trial (conducted at the Liggins Clinical Research Unit) this full trial is envisaged to be set up and performed at the “Starship Children's Health” Hospital, Auckland.

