**Table 1: Study Schedule**

|  | **Visit** | **Baseline (B)** | **Complementary Feeding 1 (CF1)**  **(4 – 6 months)** | **Complementary Feeding 3 (CF3)**  **(9 months)** | **Complementary Feeding 6 (CF6)**  **(12 months)** |
| --- | --- | --- | --- | --- | --- |
| **QUESTIONNAIRE** | Q: Mother Profile | x |  |  |  |
|  | Q: Mother Health | x |  |  |  |
|  | Q: Mother Nutrition | x |  |  |  |
|  | Q: Father Health | x |  |  |  |
|  | Q: Family Demographics | x |  |  |  |
|  | Q: Family Exit Questionnaire |  |  |  | x |
|  | Q: Child Health | x | x | x | x |
|  | Q: Child Medications | x | x | x | x |
|  | Q: Child Nutrition and Diet (3 DWFR) | x | x | x | x |
|  | Q: Child GP/Hospital Visits | x | x | x | x |
|  | Q: Child Intervention Adherence |  | x | x | x |
|  | Q: Child Respiratory Infections | x | x | x | x |
| **MEASURES** | M: Child Length | x | x | x | X |
|  | M: Child Weight | x | x | x | x |
| **SAMPLE** | S: Mother Breast Milk | x | x | x | x |
|  | S: Child Venous Blood* |  | x |  | x |
|  | S: Child Saliva Swab | x | x | x | x |
|  | S: Child Urine | x | x | x | x |
|  | S: Child Stool | x | x | x | x |

***** Opt in/out

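### Stool and urine at 7.5 months and plasma at 9 months are named in the text but absent from the visit schedule, which allows at most three of Milestone 4's four stools

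*Protocol*

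**What the plan says.** **Ages in the text.** The Stools paragraph states: "Faecal samples will be collected at 6, 7.5, 9 and 12 months of age according to a pre-defined protocol". The multi-omics section lists the same four ages for microbial profiling. The Urine paragraph gives "6, 7.5, 9 and 12 months for global metabolite profiling". The paragraph that follows the Blood bullets says that "total antibody titres in plasma will be assessed at 6, 9 and 12 months as a non-specific measure" of protective antibody. Saliva is set at 6, 9 and 12 months. Breast milk is set at baseline, 6, 6.7, 9 and 12 months.

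**Visits in the schedule.** The Data Collection text, Table 1, Table 2 and Figure 1 agree on four visits: baseline, CF1, CF3 and CF6. Figure 1 puts baseline at 2-3 months; the other three are at 4-6, 9 and 12 months. The heading directly above the stool ages reads "Stools (baseline, CF1, CF3, and CF6"). On blood, the text says "Specific consent will be sought to collect two blood samples (CF1 and CF6"). The Table 1 row "S: Child Venous Blood" is marked at those two visits only and flagged as optional.

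**The milestone.** Under Clinical Pilot Study Objectives and Milestones, Milestone 4 of the outcome-feasibility objective concerns "collecting 4 faecal samples between 6 and 12 months of age (number collected").

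**The concern.** The protocol gives two incompatible sampling plans. The 7.5-month age occurs three times (stool, urine, microbial profiling), and the milestone's count of four stools between 6 and 12 months fits that plan. Tables 1 and 2, from which site staff would normally work, have no such collection.

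Whether the planned samples can be obtained is one of this study's primary objectives. If stools are collected by the tables and counted against the milestone, the result falls short even when every family complies. That shortfall could be read as parental non-compliance and carried into the design of the later randomised trial. Early microbiome resolution is also at stake: without 7.5 months, no stool is scheduled between CF1 and 9 months. The 9-month plasma titre is named as a measurement without a blood draw to supply it.

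**Working it through.** The check is a count of scheduled collections.

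**Inputs**
- Infants: 40 (Trial Design).
- Visits: B at 2-3 months (Figure 1); CF1 at 4-6, CF3 at 9 and CF6 at 12 months (Data Collection, Table 1).
- Stool at all four visits; blood at CF1 and CF6 (Tables 1 and 2).
- Milestone 4: four stools per infant between 6 and 12 months.

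**1. Does the timeline hold an unlisted visit?** The monthly counts in Figure 1 are 8+8+8+16+16+8+16+16+8+16+16+8+8+8 = 160. Four visits for 40 infants give 40 × 4 = 160. The totals match, so there is no fifth visit.

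**2. Stools implied by the milestone.** 4 × 40 = 160.

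**3. Stools that the schedule places between 6 and 12 months.** Baseline is outside the window. CF3 and CF6 are inside. CF1 is inside only if it takes place at 6 months.

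| CF1 timing | In-window stools per infant | Total for 40 | Share of 160 |
|---|---|---|---|
| At 6 months for all | 3 | 120 | 75% |
| Before 6 months for k infants | 2 for those k, 3 for the rest | 3 × (40 − k) + 2k = 120 − k | between 50% and 75% |
| Before 6 months for all (k = 40) | 2 | 80 | 50% |

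No row reaches four per infant.

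**4. Where does CF1 fall?** In Figure 1 each visit is three months after the one before. Counting forward from a baseline at 2-3 months puts CF1 at 5-6 months. Counting back from CF3 at 9 months puts it at 6 months, and the Study Intervention section also starts the intervention at around 6 months. A value near 120 is therefore more plausible than one near 80, but the 4-6 month label leaves k open.

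**5. Would a 7.5-month collection close the gap?** With CF1 at 6 months, the in-window ages become 6, 7.5, 9 and 12: 4 per infant, 160 in total. This reproduces the milestone, so its four appears to come from the ages in the text and not from the visit tables.

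**6. Plasma.** The text needs three ages, 3 × 40 = 120 samples. The schedule allows at most 2 × 40 = 80, and fewer in practice because blood is optional. None is scheduled at 9 months.

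**7. Other specimens.** Breast milk has five ages in the text against four visits. Saliva has three ages in the text against four visits in its heading and in Table 1.

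**The case against.** **Do the tables outrank the text?** A reader might infer that the 7.5-month samples will never be taken. The documents do not establish that. The text orders them outright, parents collect stool and urine with supplied kits, and monthly contacts may be face to face. Table 1 is also not exhaustive: the monthly questionnaires and daily illness records have no entry of their own. This stands as a limit on certainty. On the other side, Table 2 is the sample plan and omits 7.5 months, the Stools paragraph has parents bring the sample to a booked clinic appointment, and the monthly contacts are described as collecting questionnaire data only. The contradiction remains; loss of the samples is not certain.

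**Is Milestone 4 failed by construction?** That too is a tempting inference, but the milestone is a descriptive count with no pass threshold, so it can be reported whatever the number. It also covers stool only; no milestone asks for 7.5-month urine or 9-month plasma.

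**Is the ceiling 50%?** Only if every infant's CF1 falls before 6 months, which Figure 1 and the stated start of the intervention make unlikely.

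**Does microbial profiling collapse without 7.5 months?** No. The plan is to profile first and then choose at least two time points for metagenomics, which can be done with 6, 9 and 12 months. What is at risk is early resolution.

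**Could the four ages be the four visits under other labels?** That needs baseline at 6 months and CF1 at 7.5 months, which the Data Collection text, Figure 1 and Table 1 contradict.

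**Does 9-month saliva stand in for 9-month plasma?** No. Saliva is planned for vaccine-specific antibody, the plasma item for total titres.

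**Conclusion.** The point holds as an internal contradiction that makes the plan wrong as written. Under the visit schedule at most 3 stools per infant (120 of 160) fall between 6 and 12 months, less one for each infant whose CF1 is before 6 months, so the four-sample count cannot be reached. No 9-month plasma is scheduled although a titre at that age is stated. These counts assume 40 infants, full compliance, baseline at 2-3 months, and samples taken only at the tabulated visits.

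The consequence is limited. A number can still be reported for Milestone 4, and profiling can still proceed. The main harm is misreading a schedule-made ceiling as poor compliance in a study meant to measure feasibility, together with the chance that staff following the text and staff following the tables collect different samples. Samples not taken cannot be recovered later, so this should be settled before enrolment.

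**What to change.** Reconcile the Stools, Urine, Saliva, Breast Milk, plasma and microbial profiling text with Tables 1 and 2, Figure 1 and Milestone 4, so that there is one schedule. Choose one of two routes for stool and urine:

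- **(a) Keep 7.5 months.** Add it to Tables 1 and 2 as a parent-collected stool and urine sample with a stated drop-off. Leave Milestone 4 at four, with the CF1 stool timed at about 6 months. The in-window target is then 4 × 40 = 160.
- **(b) Drop 7.5 months.** Delete it from the stool, urine and microbial profiling text. Restate Milestone 4 as three stools between 6 and 12 months (CF1, CF3, CF6), and report the 2-3 month baseline stool separately. The target is then 3 × 40 = 120. Simply listing baseline, CF1, CF3 and CF6 to keep a count of four would abandon the milestone's age window.

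Under either route, the 4-6 month label for CF1 has to be reconciled with the 6-month lower limit of the window. This concerns when the sample is taken and implies nothing about when feeding should start.

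Report the number collected over the number scheduled at each visit, so that schedule and compliance are not confused. Limit plasma total titres to CF1 and CF6, matching the two draws for which consent is sought, and state openly that the 9-month total titre is dropped and that saliva does not replace it. Align the saliva and breast-milk ages, including 6.7 months, to the same visits.

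Route (b) costs only wording. Route (a) adds one home collection of stool and urine per infant (40 of each), using equipment that the protocol already supplies, plus the drop-off arrangement.

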**Figure 1: Study Timeline**

|  | **Year 1** | | | | | | **Year 2** | | | | | | | | | | | | | | **Year 3** | | | |
| --- | --- | --- | --- | --- | --- | --- | --- | --- | --- | --- | --- | --- | --- | --- | --- | --- | --- | --- | --- | --- | --- | --- | --- | --- |
| **Month** | **Sep-17** | **Oct-17** | | **Nov-17** | | **Dec-17** | **Jan-18** | **Feb-18** | **Mar-18** | **Apr-18** | **May-18** | **Jun-18** | **Jul-18** | **Aug-18** | **Sep-18** | **Oct-18** | | **Nov-18** | | **Dec-18** | **Jan-19** | **Feb-19** | **Mar-19** | **Apr-19** |
| **1^st^ group**  (8 infants) |  | | | | | |  | B (8) |  | | CF1(8) | | | CF3(8) | | | | CF6(8) | |  | | | |  |
| **2^nd^ group**  (8 infants) |  | | | | | |  | | B (8) |  | | CF1(8) | | | CF3(8) | | | | | CF6(8) |  | | |  |
| **3^rd^ group**  (8 infants) |  | | | | | |  | | | B (8) |  | | CF1(8) | | | CF3(8) | | | | | CF6(8) |  | |  |
| **4^th^ group**  (8 infants) |  | | | | | |  | | | | B (8) |  | | CF1(8) | | | | CF3(8) | | | | CF6(8) |  |  |
| **5^th^ group**  (8 infants) |  | | | | | |  | | | | | B (8) |  | | CF1(8) | | | | | CF3(8) | | | CF6(8) |  |
| **Number per month** |  | | | | | |  | **8** | **8** | **8** | **16** | **16** | **8** | **16** | **16** | | **8** | | **16** | **16** | **8** | **8** | **8** |  |
|  |  | | | | | | Recruitment | | | | | |  |  |  | |  | | Sample Analyses | | | | | Data Analyses |
| Key time points |  | |  | | Ethics submission |  |  |  |  |  | First infants CF1 |  |  |  | Last infants CF1 | |  | |  | Last infants CF3 |  |  | Last infants CF6 |  |

B: Baseline enrolment (2- 3 months of age)

CF1: Complementary Feeding Intervention Begins

Food ingredient based on literature search (kumara)

Positive control (prebiotic)

CF3: Complementary Feeding Data Collection

CF6: Complementary Feeding Data Collection

**Table 1: Study Schedule**

|  | **Visit** | **Baseline (B)** | **Complementary Feeding 1 (CF1)**  **(4 – 6 months)** | **Complementary Feeding 3 (CF3)**  **(9 months)** | **Complementary Feeding 6 (CF6)**  **(12 months)** |
| --- | --- | --- | --- | --- | --- |
| **QUESTIONNAIRE** | Q: Mother Profile | x |  |  |  |
|  | Q: Mother Health | x |  |  |  |
|  | Q: Mother Nutrition | x |  |  |  |
|  | Q: Father Health | x |  |  |  |
|  | Q: Family Demographics | x |  |  |  |
|  | Q: Family Exit Questionnaire |  |  |  | x |
|  | Q: Child Health | x | x | x | x |
|  | Q: Child Medications | x | x | x | x |
|  | Q: Child Nutrition and Diet (3 DWFR) | x | x | x | x |
|  | Q: Child GP/Hospital Visits | x | x | x | x |
|  | Q: Child Intervention Adherence |  | x | x | x |
|  | Q: Child Respiratory Infections | x | x | x | x |
| **MEASURES** | M: Child Length | x | x | x | X |
|  | M: Child Weight | x | x | x | x |
| **SAMPLE** | S: Mother Breast Milk | x | x | x | x |
|  | S: Child Venous Blood* |  | x |  | x |
|  | S: Child Saliva Swab | x | x | x | x |
|  | S: Child Urine | x | x | x | x |
|  | S: Child Stool | x | x | x | x |

***** Opt in/out

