# **STUDY METHODS/DESIGN**

Ethical Considerations

Ethical approval will be obtained from The Northern B Health and Disability Ethics Committee (HDEC) of the Ministry of Health, New Zealand (HDEC reference number TBC).

Trial Design

Nourish to Flourish is a non-randomised clinical pilot study with an active control involving 40 infants (and mothers) which will examine the feasibility of conducting a randomised controlled clinical trial (RCT) to support immune protection against infection. This study will be conducted in Auckland, New Zealand. The study outline is shown in **Figure 1**.

Participant characteristics

Eligible study participants for the feasibility study are 40 healthy infants 2 to 3 months of age with the expectation that they will be introduced to their first complimentary foods around 6 months of age, and not before 4 months of age, as per the Ministry of Health Food and Nutrition Guidelines (Ref).

Infants will be ineligible for enrolment if they: were born <32 weeks’ gestation; have a developmental disability (i.e., autism, intellectual disability); an illness likely to influence their nutritional status (e.g., a chronic illness known to cause malabsorption, digestive or metabolic disorders); who have a doctor-diagnosed cow’s milk allergy; have health conditions that affect feeding; are undergoing treatment with antibiotics; are receiving a supplement with a pre- and/or probiotic; or whose parents written or spoken English comprehension is likely to make participation difficult for them. The decision to participate and written, informed consent will be obtained by the research team from parents/guardians on the child’s behalf. Infants who were born premature or small for gestational age will also be excluded as they may have special dietary requirements.

Infants will be recruited from urban central and greater areas of Auckland. Recruitment strategies include electronic and print advertising through The University of Auckland, community outreach campaigns including coffee groups, antenatal groups, local newspapers, and appropriate social media platforms.

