**Ethical Considerations**

Participation in the study is entirely voluntary. All caregivers (parent or legal guardian) of the participants will be provided with written informed consent. The Informed Consent Form will be signed and dated by the caregiver before they enter the study or undergo the any intervention related to the study. The Investigator or their nominee will explain the details of the trial and provide a Participant Information Sheet, ensuring that the caregiver has had sufficient time to consider their infant participating or not. The Investigator will answer any questions that the caregiver has concerning study participation. The investigator or their nominee shall emphasise to them that consent regarding study participation may be withdrawn at any time without penalty or affecting the quality or quantity of their future medical care, or loss of benefits to which the participant is otherwise entitled.

One copy of the consent will be kept by the caregiver, and one will be kept by the Investigator. The trial will not be initiated before the protocol, informed consent forms and participant information sheets have received approval / favourable opinion from the NZ Health and Disability Ethics Committee (HDEC).

The process for obtaining participant informed consent will be in accordance with the REC guidance, and Good Clinical Practice (GCP) and any other regulatory requirements that might be introduced. The investigator or their nominee and the participant or other legally authorised representative shall both manually sign and date the Informed Consent Form before the person can participate in the study.

The decision regarding participation in the study is entirely voluntary. The investigator or their nominee shall emphasize to them that consent regarding study participation may be withdrawn at any time without penalty or affecting the quality or quantity of their future medical care, or loss of benefits to which the participant is otherwise entitled. No study specific intervention will be done before informed consent has been obtained.

If the Informed Consent Form is amended during the study, the investigator shall follow all applicable regulatory requirements pertaining to approval of the amended Informed Consent Form by HDEC and use of the amended form (including for ongoing participants).

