This feasibility study will determine the power for a subsequent RCT there no sample size calculations are required. The proposed sample size of 30 infants who will receive the feeding intervention and 10 infants will receive the active control (probiotic) for a period of 6 months. This sample target is based on an achievable recruitment rate of participants within a 12 month time frame and allows for follow up for 6 months.

In addition to classical case/control analyses, every infant will not only be sampled but also analysed before and after the prebiotic feeding, i.e. being assessed as a case/control pair, in addition to classical data analysis. This “personal” case/control pairwise analysis will account for differences in infant feeding before the actual intervention (e.g. duration of breast feeding, infant formula differences) and can be interpreted as a multiplexed n-of-1 trial.

The feasibility aspect of this study will assess compliance and rate of loss to follow up. This data will be used to inform a subsequent RCT. In previous studies and prevalence studies that we have conducted in 12 to 24 month old children the recruitment rate has been approximately 2 participants per week.

Statistical methods

A multiplexed n-of-1 clinical design trial design in which every infant is sampled before and after the intervention, and followed up. Thereby constituting its own case-control pair.

Data Management

Each participant will be assigned a trial identity code which will be allocated at enrolment to allow for link-anonymisation of data. The documents and database will also use infant date of birth. All personal data will be stored on an encrypted drive with links to personal information only being available to the study co-ordination team. Paper forms and hard copies will be stored in locked filing cabinets in secure sites. Data will be consolidated by each site using the REDCap (Research Electronic Data Capture) software (RW.ERROR - Unable to find reference:1572). This is a secure web application which is password protected and not accessible by third parties. REDCap will be managed at the University of Auckland. The investigator will also keep a screening log with details of all participants screened for the trial with their name, date of birth, NHI number, and trial number. The investigators will permit monitoring, audits, review, and regulatory inspections, providing direct access to source data/documents (where appropriate).

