All measures and entered data are double-checked against source documents. Trained personnel will conduct the study according to standard operating procedures and protocols. All incidents or deviations from the protocol will be documented. A major violation is defined as one that may impact subject safety, affect integrity of the study data and/or subject’s willingness to participate in the study. This is a serious discrepancy resulting from error, fraud or misconduct e.g. failure to obtain informed consent or a breach in randomisation procedures. Should a major violation occur HDEC will be notified. Adverse events will be reviewed by an internal clinician; should any events be deemed as concerning for the health of the child they will make a decision as to whether the child’s GP needs notification (if consented to do so) or in more extreme cases, will withdraw the child from the study and make recommendations for clinical care. Should caregivers (parent or legal guardians) not wish to provide GP details, the clinician will contact them directly in situations deemed necessary in his medical opinion. All essential documents, including source documents will be retained for a minimum period of 10 years following the end of the study.

Data Analysis

Integrated analysis of the multi-omics data from multiple platforms will be performed to visualise and interpret changes according to biological pathways and networks. This will be performed using software tools such as Ingenuity Pathway Analysis (IPA), mixOmics [Le Cao 2009], and metaCyc [Caspi 2014]. In additional to classical case/control analyses, every infant will not only be sampled but also analysed before and after the “prebiotic” feeding, i.e. being assessed as a case/control pair, in addition to classical data analysis. This “personal” case/control pairwise analysis will account for differences in infant feeding before the actual intervention (e.g. duration of breast feeding, infant formula differences) and can be interpreted as a multiplexed n-of-1 trial [24].

Clinical Pilot Study Objectives and Milestones

1. To determine whether infants will consume the target food(s) in a dose estimated to be sufficient to impact protection against infection *via* modification of the microbiome and associated metabolite changes.
2. Milestone 1: Amount of the candidate food(s) free-living infants are offered and consumed over the complementary feeding period (6 to 12 months of age).

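### The exit questionnaire is scheduled only at 12 months and no exit contact is provided for families who leave earlier, so burden feedback as scheduled comes only from families who complete follow-up

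*Protocol*

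**What the plan says.** In the protocol's Table 1 (Study Schedule), the row "Q: Family Exit Questionnaire" has a single mark, under CF6 at 12 months. The cells for baseline, CF1 and CF3 are empty.

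The Questionnaires paragraph under Data Collection states the purpose: "Brief exit interviews will determine participant burden and suggestions to improve engagement with the intervention". That sentence gives no time point. The paragraph's heading lists the visits as "baseline, CF1, CF3, CF6", with no early-withdrawal visit. The monthly contacts described just above it "will collect information on the dietary intervention adherence and recent health history"; burden and reasons for leaving are not named.

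Early exit is foreseen in two places. Under Ethical Considerations, "consent regarding study participation may be withdrawn at any time". Under Data Management, after review of adverse events the clinician in extreme cases "will withdraw the child from the study and make recommendations for clinical care". Neither place mentions an exit questionnaire or interview.

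Under Sample Size the protocol says: "The feasibility aspect of this study will assess compliance and rate of loss to follow up". It adds that these data will inform the later randomised trial. Recording why families leave is not mentioned.

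**The concern.** The exit interview is the only instrument to which the protocol assigns the question of burden. A family enrols when the infant is 2 to 3 months old and is first scheduled to be asked at 12 months. In between it keeps daily illness records and weighed food records, is invited to consent to blood draws, and supplies stool, urine, saliva and, where possible, breast milk at repeated visits. Families who find this too much are the ones most likely to leave, and they also know most about what should change. The schedule does not reach them.

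At stake is how useful the pilot is for designing the randomised trial. A dropout rate without reasons says how many families to expect to lose, but not whether the food, the sampling, the records or something unrelated drove the loss. No later analysis can recover answers that were never collected, so this belongs in the protocol's data collection and cannot be left to an analysis plan.

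**Working it through.** The protocol states no figure to reproduce. The check sets its provisions side by side and then bounds the possible effect. I take the exit interview in the text and the exit questionnaire in Table 1 to be the same contact.

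**Who reaches the questionnaire**

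| Family's course | Reaches CF6? | Exit questionnaire as scheduled? |
|---|---|---|
| Stays in follow-up, keeps giving the food | Yes | Yes |
| Stays in follow-up, stops giving the food | Yes (nothing says that stopping the food ends participation) | Yes |
| Caregiver withdraws, or contact is lost, before 12 months | No | None provided |
| Child withdrawn by the clinician before 12 months | No | None provided |

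The gap is therefore about leaving the study, not about stopping the food.

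**Time at risk.** Enrolment is at 2 to 3 months and CF6 at 12 months: 12 − 3 = 9 and 12 − 2 = 10. A family has about 9 to 10 months in which to leave before the only scheduled exit contact.

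**Bounds on the effect.** Inputs:
- N = 40, from Trial Design ("active control involving 40 infants").
- Dropout: not given. I assume 10%, 20% or 30%, so d = 4, 8 or 12 families lost.
- Share of interviewed families reporting high burden: not given. I assume 25%, so x = 0.25 × (40 − d).

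Nothing is assumed about the views of those who left. If none of them found the burden high, the share among all 40 is x/40. If all of them did, it is (x + d)/40.

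| Dropout | Left (d) | Interviewed | High burden (x) | Lowest, x/40 | Highest, (x + d)/40 |
|---|---|---|---|---|---|
| 10% | 4 | 36 | 9 | 9/40 = 22.5% | 13/40 = 32.5% |
| 20% | 8 | 32 | 8 | 8/40 = 20% | 16/40 = 40% |
| 30% | 12 | 28 | 7 | 7/40 = 17.5% | 19/40 = 47.5% |

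The interviewed families give 25% in every row. The width of the interval is d/40, the dropout rate itself. The interval extends further above 25% than below it: at 20% dropout, 15 points above and 5 below.

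**The case against.** Four points can fairly be made against this.

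- **Timing is not closed.** The exit-interview sentence has no time point and is not limited to completers, and Table 1 has columns only for planned visits. Staff could hold the interview whenever a family leaves. This stands to the extent that a reader who infers that early leavers can never be asked goes further than the documents. But the only timing the protocol states is CF6, and a team following the schedule would not ask earlier.
- **Giving up on the food is captured.** A reader might infer that families who abandon the food are also missed. The documents do not support that. Those who remain in follow-up still reach CF6, and their adherence is recorded by the monthly contacts, by daily retrospective questionnaires, product counts and photographs, and by the adherence questionnaire at CF1, CF3 and CF6. This stands in full.
- **Burden is not a listed objective or milestone.** The milestones concern intake, completion of records and samples, recruitment and adverse events, and these can include data from families who later leave. This also stands. It would be too strong to say that the trial would be designed only on the views of families for whom the procedures worked. Burden is nevertheless a stated purpose of the exit interview, and it helps explain the compliance and attrition that the pilot measures.
- **Size and direction are not established.** The bounds include no bias and bias the other way. Giving leavers a higher assumed burden than completers would produce a definite figure, but only by building in the conclusion. For clinician withdrawals, the adverse-event review would already show the reason.

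**Conclusion.** The point holds as a scheduling gap. The only stated time for the exit questionnaire is 12 months, and no exit contact is provided for families who leave before then. The reasons behind the loss to follow-up are not scheduled to be collected either. Burden feedback obtained as scheduled will represent families who complete follow-up.

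It is likely to understate burden, on the assumption that staying to 12 months depends partly on tolerating the procedures. That is plausible but not shown by the documents. The size cannot be derived without a dropout rate. The bounds above are illustrations on assumed dropout and an assumed 25%, and they show only that the room for error grows in step with attrition.

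The protocol does not contradict itself here, and the milestone counts are not invalidated. This is an inexpensive improvement to a stated schedule entry, worth making because the missing information cannot be recovered later.

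**What to change.** In Table 1, change the timing of the Family Exit Questionnaire from CF6 alone to CF6 or withdrawal/last contact, whichever comes first. Add a matching sentence to the Questionnaires paragraph. For early leavers, offer it by telephone, a route the protocol already uses for the monthly questionnaires, and make clear that answering is voluntary. Record the main reason for leaving in a few categories, such as food, sampling, record-keeping or other. Report burden separately for completers and early leavers, with the number of leavers who were approached and the number who answered.

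The cost is one line in the table, one sentence in the text and one short call per early leaver: 4 to 12 calls under the dropout rates assumed above. No visit is added. Some leavers will decline or be unreachable, so the information will be partial, and the reported response count will show how partial.
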